## Intervention

4

Parent-child dyads from each site will be randomly assigned to GSH delivered in the primary care setting or FBT delivered in an academic setting. Two large pediatric practices in San Diego County (specifically located in Chula Vista and Escondido, where rates of childhood OW/OB are 38% and 39% respectively) were recruited to participate in this study. Families randomized to GSH will attend 14 sessions (4 consecutive weekly meetings, and then 10 sessions every other week) spanning a 6-month period. Each session will be 20 min in length except for the first session which can last up to an hour, and both parent and child will attend these sessions. During the session, health coaches will answer any questions about healthy dietary and physical activity behaviors, assist parents with problem-solving, and promote accountability.

Families randomized to FBT will attend 16 weekly sessions and then 4 sessions every other week for a 6-month period. Each session lasts 60 min and are conducted in a group format where parents attend one group and children attend another group. Content of the child group mirrors that of the parent group except that information is delivered in a developmentally appropriate format for children. The same information is provided in both GSH and FBT and cover the core nutrition concepts, physical activity behaviors, and basic behavioral strategies that are effective in weight loss. Intervention topics are listed in Table 2. The overall goal of this program is to help children improve their weight status by losing ½ to 1 lb per week [12]. Parents interested in losing weight are also encouraged to do so since parent weight loss is highly correlated with child weight loss [44].

**Table 2 tbl2:** FBT vs. GSH session topics.

Week #	FBT Session #	FBT Topic	GSH Session #	GSH Topic
1	1	Introduction	1	Introduction
2	2	Dietary Changes	2	Dietary Changes
3	3	Stimulus Control/The Home Environment	3	Stimulus Control/The Home Environment
4	4	Physical Activity	4	Physical Activity
5	5	Problem Solving	–	–
6	6	Positive Parenting/The Rewards System	5	Motivation System and Parenting Skills
7	7	Lifestyle & Sedentary Behaviors	–	–
8	8	Problem Solving around High-Risk Situations	6	Team Building
9	9	Motivation	–	–
10	10	Team Building	7	Problem Solving
11	11	Review	–	–
12	12	Behavior Chains	8	Behavior Chains
13	13	Body Image & Teasing	–	–
14	14	Tricky Hunger & Emotional Eating	9	Emotional Eating
15	15	Shopping on a Budget	–	–
16	16	Meal Planning	10	Shopping on a Budget and Meal Planning
17	–	–	–	–
18	17	High Risk Situations	11	Lifestyle & Sedentary Behaviors
19	–	–	–	–
10	18	Social Support and Sabotage	12	Body Image & Teasing
21	–	–	–	–
22	19	Relapse Prevention	13	Social Support
23	–	–	–	–
24	20	Graduation	14	Relapse Prevention

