### Trial design

3.1

GOTDoc is a two-arm, parallel assignment, pragmatic clinical trial, using a randomized control design, comparing GSH delivered in the primary care setting to traditional FBT delivered in an academic center. The intervention will be implemented in the Children's Primary Care Medical Group of San Diego (CPCMG). Two CPCMG sites with 6 providers at each site were identified in San Diego that have similar socio-economic and ethnic/racial demographic characteristics among their patient population. Parent and child will be randomized within each clinic at a one-to-one ratio to receive GSH at the clinic or intensive FBT for weight loss at CHEAR. Randomization will occur at the level of the individual, allowing us to eliminate the effect of the provider on treatment effects. Randomization will also be stratified by child sex to ensure equal distribution between groups. Assessments will occur at baseline, post-treatment (month 6), and 6-month follow-up (month 12). The primary outcomes of this study are attendance and change in BMI percentile/z-score. Secondary outcomes are change in child lifestyle behaviors, parent support behaviors, and parent self-efficacy and empowerment to make behavior change. We will also examine the cost-effectiveness of the GSH model of treatment on changes in child BMI percentile/z-score.

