
### Intervention group: Guided Self-Help for pediatric weight loss

4.2

The GSH intervention will include 14 sessions over 6 months to mimic the structure of the proposed Medicare funding for obesity treatment for adults (www.cms.gov). These sessions will last 20 min, except for the first session which can last up to an hour, and take place in the clinic. During the first session, the family will receive a parent treatment manual and an age-appropriate child manual that covers several nutrition and physical activity topics as well as behavioral strategies. During the first treatment meeting, manuals are provided to families, and they are instructed to read each chapter prior to the next meeting. The purpose of the manual is to provide key components of gold-standard family-based behavioral therapy (FBT) [[48], [49], [50]] for childhood obesity in a self-help format. Parent manuals emphasize changing the behaviors of the family, and child manuals emphasize changing their own behaviors, in an age-appropriate manner.

In the first session, the health coach will review the structure of future meetings, review how to complete self-monitoring diaries, and set goals with the families. During subsequent sessions, the health coach will assess patient/parent readiness to engage in behavior change, assess barriers and facilitators to behavior change, engage in behavior change and problem solving, and provide feedback and accountability. The goals of the 20-min meetings are to: a) measure the child and parent's weight and reflect with the parent/child dyad on any eating or physical activity changes that may have influenced weight change (either up or down) between visits; b) clarify the content of the manuals; c) use problem-solving to address barriers to implementation of the behavioral strategies outlined in the manual; d) reinforce effort and success; and e) encourage parents and children to try new behavioral techniques. Parents and children will meet together with the health coach during these 6 months.

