### Treatment fidelity

4.4

Health coaches for the GSH intervention and parent and child group leaders in FBT are marriage and family therapy trainees or masters level students. The majority of the staff and health coaches were also bilingual and bicultural. All health coaches attended a one-day training with experts in the field of pediatric weight loss ([name], [name]). These trainings reviewed current information regarding nutrition, physical activity, and behavioral strategies for weight loss, and protocols for delivering FBT and GSH. Health coaches were given treatment manuals and protocols in order to maintain treatment fidelity and quality of care. Prior to the start of the intervention, health coaches shadowed a skilled health coach delivering the program to currently enrolled subjects. During the intervention, all sessions will be audiotaped and 10% of tapes will be reviewed during weekly supervision. During the intervention, health coaches have access to both investigators and research assistants via e-mail and phone should any emergent questions arise in the office.

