## Data analysis

5

5.1. This study is a pragmatic randomized control trial using a one-to-one randomization ratio within each clinic, randomizing at the level of the individual. First, we will track the number of sessions each family attended within each group and examine if there is a difference in the proportion of sessions attended between groups using a generalized linear model (binomial family). For our second primary outcome, we will estimate between-group differences (GSH vs FBT) in BMI percentile/z-score (our second primary outcome) over 6- and 12-month assessments using linear mixed effects (LME) analysis adjusting for corresponding baseline BMI percentile/z-score values. BMI z-score is calculated using the formula: [(BMI/M)^L^ −1]/(L x S). (M = median; L = power in the Box-Cox transformation; S = generalized coefficient of variation; values vary based on age in months of the child) All models will adjust for standard patient characteristics (age, race/ethnicity, sex, insurance type) as planned covariates and any differential effects across clinics (i.e., main effect rather than random effect given limited number of clinics).

As a secondary analysis, we will assess the degree to which treatment assignment (GSH vs. FBT) was associated with change in proposed mediators (considered outcomes in these analyses) including child lifestyle behaviors (e.g., eating and physical activity behaviors), parent self-efficacy, parent empowerment, and parent support behaviors (e.g., parent monitoring, adherence to treatment recommendations) using LME models. For mediation modeling, we first will estimate the effect of allocation on a change in proposed mediators (path ‘a’) at 6-months with adjustment for corresponding baseline values. If significant, we will then add baseline and 6-month terms for mediators to the LME model examining their relationship to the primary outcome of BMI percentile/z-score. The indirect effect of group allocation on BMI percentile/z-score through changes in mediators (path ‘b’) will be computed using a product of coefficients method (path ‘a*b’) along with bootstrap confidence intervals. As an adjunct to the primary analyses, we will also explore attendance patterns using a cox proportional hazards regression model to examine predictors of attrition, defined as missing 3 or more consecutive sessions.

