5.3. Power Analysis: For this trial, sample size estimates took attrition into account. Our first primary hypothesis is that a greater proportion of families in the intervention group will enter into and attend behavioral treatment for obesity. However, there was lack of evidence from previous studies to conduct a power analysis with this outcome. Therefore, power analyses were based on changes in BMI z-score (our second primary outcome) that was supported by observations in the GSH pilot which estimated a decrease in BMI z-score d = |1.71–1.50|/.30 = 0.667. Empirical power estimates were assessed by generating multivariate random samples that were matched to the expected BMI z-score for each condition and variability over time as observed in our pilot study. We expected decreases in BMI z-score of 0.10 among those enrolling in GSH, and a slight increase of 0.05 in BMI z-score in the usual care group. Each of 1000 simulated data sets was analyzed using a LME (random intercepts: patients within clinics) and specific output saved (e.g., standardized regression coefficients, p-values). The percentage of datasets with significant effects (i.e., p < 0.05) for the primary hypothesis comparing GSH vs. usual care provided a simulation-based estimate of power for the primary hypothesis. With a median between-group effect of −0.39 (s d. = 0.13) across 1000 data sets, the planned design would provide greater than 0.82 power for detecting the effect with allowance for up to 20% lost to follow up [72]. We allow up to 20% loss to follow-up to maintain the integrity of the sample for data analysis, and have been able to limit our loss to follow-up in previous trials to 13–18% of the sample. Given these parameters, we estimated that we would need to recruit 200 families into the trial, 100 in GSH and 100 in FBT. With a sample of 200 to support between-group comparisons of BMI percentile/z-score, we estimate we will have power >0.95 to detect a difference in the proportion of sessions attended in a generalized linear model (binomial) with two-sided alpha <0.05 given that we expect >85% attendance in GSH and 60% attendance in FBT. All analyses of primary outcomes will use an intention to treat sample with analyses of all participants who provided both baseline and post-treatment assessments.

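### FBT is delivered in groups and GSH family by family, but the stated models and power simulation have no FBT-group term, so type I error may exceed 5% and the stated power may not be met

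*Protocol article*

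**What the plan says.** **Delivery.** Section 4 describes 20 FBT sessions (16 weekly, then 4 every other week): "Each session lasts 60 min and are conducted in a group format where parents attend one group and children attend another group". Section 4.3 repeats the group format and places it at one site in La Jolla. In GSH, each family sees a coach: "Parents and children will meet together with the health coach during these 6 months" (Section 4.2). On staffing, Section 4.4 says: "Health coaches for the GSH intervention and parent and child group leaders in FBT are marriage and family therapy trainees or masters level students".

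**Randomisation.** Families are allocated 1:1 within clinic. Section 3.1 adds: "Randomization will occur at the level of the individual, allowing us to eliminate the effect of the provider on treatment effects".

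**Analysis.** Section 5.1 compares attendance "using a generalized linear model (binomial family") and BMI z-score "using linear mixed effects (LME) analysis adjusting for corresponding baseline BMI percentile/z-score values". All models adjust for age, race/ethnicity, sex, insurance type and clinic, with clinic entered as a "main effect rather than random effect given limited number of clinics".

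**Power.** Section 5.3 says: "Each of 1000 simulated data sets was analyzed using a LME (random intercepts: patients within clinics"). It reports a median standardised effect of −0.39 with standard deviation 0.13 across data sets, and power above 0.82 with up to 20% loss, from 100 families per arm. For attendance it claims power above 0.95 with more than 85% attendance in GSH against 60% in FBT.

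**The concern.** Individual randomisation makes families independent at the moment of allocation. Treatment in groups can undo that in one arm: families in the same FBT group share sessions and peers, so their outcomes may be positively correlated. The variance of the FBT mean is then larger than a model of independent families reports, while the GSH mean is not affected in this way.

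The article does deal with clustering, but only with sources that exist before randomisation: the referring provider (by individual randomisation) and the clinic (by a fixed effect). The source created by treatment has no term. The clinic effect does not absorb it, because clinic is the recruitment site and FBT families from both clinics go to the same centre.

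Both primary comparisons are at stake. Intervals could be too narrow, p-values too small, and the sample size less adequate than stated.

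**Working it through.** **Inputs from the article.** 100 families per arm, hence 80 after 20% loss; two-sided alpha 0.05; effect 0.39 with standard deviation 0.13 across simulations; stated power >0.82 (BMI z-score) and >0.95 (attendance, 85% against 60%).

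**Assumed, because the article does not give them.** Families per FBT group m = 6 to 12; ICC within FBT group 0.01 to 0.10. No clustering in GSH in the main calculation.

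**Step 1: the article's own power figures.** Taking 0.13 as the standard error, 0.39/0.13 = 3.0 and power = Φ(3.0 − 1.96) = 0.851, which agrees with >0.82. An exact reproduction is not possible, because the pilot covariance behind the simulation is not given. A plain two-sample comparison with d = 0.39 gives 0.694 at 80 per arm and 0.787 at 100. For attendance, a two-proportion test with one binary result per family gives 0.950 at 80 per arm and 0.981 at 100. All these figures assume independent families.

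**Step 2: effect of grouping in one arm.**
- Design effect in FBT: DE = 1 + (m − 1) × ICC.
- Ratio of true to model standard error, equal arms and equal variances: r = √[(DE + 1)/2].
- True type I error of the unclustered test: 2 × [1 − Φ(1.96/r)].
- Power of a correctly sized test: Φ(3.0/r − 1.96).

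| m | ICC | DE | r | Type I error | Power |
|---|---|---|---|---|---|
| any | 0 | 1.00 | 1.000 | 5.0% | 0.851 |
| 6 | 0.01 | 1.05 | 1.012 | 5.3% | 0.842 |
| 6 | 0.02 | 1.10 | 1.025 | 5.6% | 0.833 |
| 8 | 0.05 | 1.35 | 1.084 | 7.1% | 0.790 |
| 10 | 0.02 | 1.18 | 1.044 | 6.0% | 0.820 |
| 10 | 0.05 | 1.45 | 1.107 | 7.7% | 0.774 |
| 12 | 0.10 | 2.10 | 1.245 | 11.5% | 0.674 |

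**Step 3: where power reaches 0.82.** Φ⁻¹(0.82) = 0.915, so r = 3.0/(1.96 + 0.915) = 1.043. Then DE = 2 × 1.043² − 1 = 1.18 and, with m = 10, ICC = 0.18/9 ≈ 0.02.

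**Step 4: check by simulation.** Unclustered t-tests at 80 per arm, 6,000 runs per setting, gave type I error of 4.95% (ICC 0), 5.3% (m = 8, ICC 0.01), 6.1% (m = 8, ICC 0.02), 7.5% (m = 8, ICC 0.05), 7.5% (m = 10, ICC 0.05) and 10.7% (m = 10, ICC 0.10). These agree with the formula.

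**Step 5: attendance.** The per-family variances are 0.60 × 0.40 = 0.24 in FBT and 0.85 × 0.15 = 0.1275 in GSH. With m = 10 and ICC 0.05, the variance sum is 0.24 × 1.45 + 0.1275 = 0.4755, against 0.3675 under independence. Power by the unpooled normal approximation is Φ(0.25/√(0.4755/80) − 1.96) = 0.90 at 80 per arm and 0.95 at 100; under independence the same approximation gives 0.96 and 0.98. The claim of >0.95 is therefore lost at 80 per arm and left without margin at 100.

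**Step 6: coaches.** With 4 GSH coaches not shared between arms, and FBT at m = 8 and ICC 0.05, simulated type I error was 9.4% (coach ICC 0.02) and 12.3% (coach ICC 0.05). With the same 4 staff serving both arms in balance and no FBT group effect, it was 4.8% to 5.1%, so there was no inflation.

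**The case against.** **Random effects may be left to the SAP.** Section 5.1 names an LME without listing its random effects in full, and an article may leave that to a plan not shown here. This carries some weight for the BMI model. It carries less for the attendance GLM and the power simulation, which are written out without a group term. Section 5.1 also does discuss clustering, and stops at clinic.

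**Inflation is not a fact.** A reader might infer that type I error does exceed 5%. The article gives no ICC or group size. At ICC 0 there is no inflation, and at 0.01 type I error is only about 5.3% to 5.6%. Families who never attend FBT have no group exposure, which dilutes the correlation in an intention-to-treat comparison. This objection stands, so the point is conditional.

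**Cohorts are not described.** A reader might infer closed groups with fixed leaders and a common start date. The numbered topic sequence in Table 2 suggests cohorts, but no section states them. With rolling entry, a simple nested intercept would not fully describe the structure.

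**Coaches.** A reader might extend the point to GSH coaches. Section 4.4 describes one type of staff for both arms and does not say whether individuals serve both; if they do so in balance, the problem disappears.

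**Section 3.1.** The sentence on eliminating provider effects might be read as an error. In context the provider is the primary care provider, and the sentence is not wrong on that reading. It simply does not reach FBT groups.

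**Power.** At the mild end of the assumptions (m = 6, ICC 0.02) power is 0.83, which still meets >0.82. The stated power is therefore not overstated in every case.

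**Conclusion.** The concern holds in conditional form. The design is partially nested, and neither the stated analyses nor the power simulation allows for FBT groups. Any positive correlation within FBT groups makes the model standard error too small.

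The size rests on assumed inputs: 6 to 12 families per group, ICC 0.01 to 0.10, and clustering in FBT only. Across that range the true standard error is 1.01 to 1.25 times the model's, type I error is 5.3% to 11.5%, and power for BMI z-score is 0.84 down to 0.67. The central case (10 families, ICC 0.05) gives 1.107, 7.7% and 0.77. The power figures also rest on reading 0.39/0.13 as a Wald ratio.

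The documents do not support saying that type I error is certainly above 5%, or that coach clustering adds to it.

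**What to change.** - **Data:** record an FBT group ID as treatment is delivered, since it may be hard to rebuild later. Parents and children sit in separate groups, so decide in advance which grouping defines the cluster. Record coach ID as well.
- **BMI z-score:** fit the LME with a random intercept for FBT group in the FBT arm only, arm-specific residual variance, and small-sample degrees of freedom (Satterthwaite or Kenward-Roger). With 100 FBT families and 6 to 12 per group there would be only about 8 to 17 groups. State a rule for FBT families who never attend: treat them as singletons or keep them in their assigned group.
- **Attendance:** carry the same clustering into the binomial model, by a random effect or by a cluster-robust variance with a small-sample correction. The degrees-of-freedom methods for the LME do not transfer directly.
- **Power:** restate both figures with an assumed group size and ICC, and show a range.
- **Coaches:** add a coach term only if coaches are not shared between the arms.

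The cost is one or two ID variables, a rule for never-attenders and a change of model statement. Intervals will be somewhat wider and the stated power slightly lower. If the ICC proves negligible, little is lost.

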### Obesity management by the PCP prior to randomization

4.1

All clinics within the CPCMG network utilize the EPIC electronic health record (EHR) and have a basic obesity management tool for children. This tool includes: 1) alerts to physicians to address and document weight status in all children older than 2 years with OW/OB; 2) prompts to assess risk for obesity-related medical co-morbidities and relevant family history; 3) a tool to facilitate efficient assessment of parent readiness to make behavior changes; 4) a focused menu of options of strategies for weight loss; 5) alerts to obtain appropriate labs, schedule follow-up visits, and make sub-specialty referrals when necessary; and 6) links to handouts and referrals to weight loss treatment options at the tertiary care center. To determine whether parents are ready to engage in obesity treatment, the PCP (prompted by the EHR) will ask parents of all identified children 3 motivation questions: “On a scale of 1–5 with 1 being ‘not important’ and 5 being ‘very important’, how important is it for you to make changes to help your child lose weight at this time?”; “On a scale of 1–5 with 1 being ‘not confident’ and 5 being ‘very confident’, how confident are you that you can help your child lose weight at this time?”; and “On a scale of 1–5 with 1 being ‘not motivated at all’ and 5 being ‘very motivated’, how motivated are you to help your child lose weight at this time?”. These questions are based on the transtheoretical model of behavior change [45], and patients who report higher scores on these questions have reported greater success in weight loss activities [21,46,47]. Parents who report a 3 or higher on any question will be told about the study and asked if their name and contact information can be sent to the study coordinator. If the parent agrees, referrals to the study coordinator will occur via a link in the EHR and/or in person (if she is in the office that day). The study coordinator will contact the family and screen for eligibility. Once families have completed the consent process and baseline assessments, they will be randomized to the intervention (GSH) or usual care (FBT) group. Randomization will be conducted with a random number generator independent of the investigators and physicians. Participants will be informed of both intervention possibilities to ensure their commitment to both. Due to the clear differences in treatment groups, participants will not be blinded to the treatment arms.
